#### ‘SHAM’ group

Placebo stimulation will be delivered using the same modalities as in the TENS group, but with a current that automatically switches off after 5 s of stimulation.

### Outcomes

The primary outcome of the study will be the evolution of walking distance on a treadmill between before (D_0_) and after rehabilitation (D_21_), with or without TENS, measured in metres according to a standardised protocol (300-m test) [21].

The secondary outcomes of the study will be the maximal duration of walking, variation in TcPO_2_, the ABI value measured during the Strandness exercise test, variations in peak VO_2_, endothelial function (using the EndoPAT® system), cardiovascular risk factors (Body Mass Index, lipids (LDL-cholesterol, HDL-cholesterol, triglycerides), resting arterial blood pressure, glycaemic status (fasting glycaemia, glycosylated haemoglobin (HbA1c) level), and the scores obtained in the WELCH questionnaire [22].

### Blinding and randomisation

The study participants will be randomised into two balanced groups (1:1): (1) TENS and (2) SHAM. The randomisation will be stratified according to the four inclusion centers, and the two arms (TENS and SHAM) will be distributed in random-sized blocks (blocks of 2, 4 or 6). The method of randomisation used will be Ralloc on stata 9.2 S.E.

The assessor executing the measurements and the investigators will be blinded to group allocation. The statistician will be blinded until completion of the statistical analysis. Only the physiotherapists executing the cardiac rehabilitation programme will be aware of the assigned group of randomisation. Physiotherapists will not participate to the baseline or final measurements.

Participants will be blinded regarding the randomisation group to which they belong. The physiotherapists will install the TENS device and electrodes and will programme the TENS unit (pulse width, frequency, and intensity) according to the TENS or SHAM group (using a current that automatically switches off after a few seconds of stimulation).

### Measurements (before and after 3 weeks of the cardiovascular rehabilitation programme)

#### 300-m treadmill test

This walking test on a constant-intensity treadmill (300-m test) to measure walking distance (principal judgement criterion) is a procedure which is used for the rehabilitation of PAD patients and that has been described by our team to evaluate patients’ walking potential [21, 23]. For this test, the speed and the slope of the treadmill are initially adjusted in such a way to make claudication develop at a distance of 300 m. Five successive walking pre-tests (with periods of passive recovery of 5 min between tests) are necessary to obtain these treadmill settings with a baseline speed of X km/h and a baseline slope of X%. Once these parameters have been established, they will be kept constant for all of the pre- and post-treatment evaluations. This will allow us to determine the improvement in walking distance. During the test, the distance covered will be hidden from patients so as not to modify their performance. Each evaluation will consist of five successive tests with 5 min of passive recovery between the tests. The pre-test will take place at least 1 h before the initial test.

*The constant intensity effort test on a treadmill (Strandness exercise test)* will be supervised by a therapist in a room devoted to rehabilitation on a treadmill conducted according to the protocol described by Strandness [24]. The test starts by measuring ankle blood pressure at rest. The walking speed is constant (2 mph or 3.2 km/h) and the slope is fixed at 10%. This procedure, which has been validated and is classically used for the rehabilitation of PAD patients, allows a quantitative and reproducible evaluation of the haemodynamic repercussions related to PAD. The walking test is generally stopped when the subject can no longer continue (pain in the lower limbs). The test ends with the measurement of blood pressure at the ankle just after the exercise.

*The cardiorespiratory maximal effort test* will be supervised by a cardiologist in a room devoted to bicycle ergometer exercises. After a 3-min rest phase with the patient sitting on the apparatus and a 2-min warm-up phase at 20 W, the workload will be progressively increased by 15 W every minute until the maximal capacity of the patient has been reached according to the classical recommendations in the academic literature [25]. The imposed pedalling frequency will be between 60 and 70 rotations per minute (rpm). The exercise will be conducted until exhaustion of the subject, whatever the reason for stopping. The test will end with an active (2 min at 30 W) and then a passive recovery phase (4 min without load sitting on the apparatus). During this test, the subjects will be continuously monitored with a 12-lead electrocardiogram and by measuring arterial blood pressure in a relaxed arm every 2 min. Pulmonary gas exchange and the ventilatory responses will be measured continuously using an automated ‘breath-by-breath’ gas analysis system. Arterial oxygen saturation will be recorded throughout the maximal effort test using a pulse oximeter. The test can be stopped by the cardiologist in cases of cardiac intolerance to effort (severe arrhythmia, poorly controlled arterial hypertension, significant myocardial ischaemia, etc.). In such cases the patient will be excluded from the research protocol.

### Measurement of endothelial function (using the EndoPAT® system)

Plethysmography probes will be placed on the index fingers of both hands. Each probe includes a latex membrane which is inflated by a micro-compressor incorporated in the device, and a pressure close to diastolic arterial blood pressure is maintained. The probes thus fit the finger perfectly and measure variations in pulse-wave amplitude which reflects variations in capillary blood volume. The protocol consists in carrying out a 5-min ischaemia test of one of the two forearms by complete occlusion of the brachial artery by inflating a cuff to 60 mmHg above the systolic arterial blood pressure to a minimum of 200 mmHg. The amplitude of the pulse wave is recorded continuously on both sides for 15 min: 5 min before occlusion (baseline), during the 5 min of occlusion (ischaemia) and during the first 5 min post occlusion (hyperaemia). The RH-PAT (Reactive Hyperaemia-Peripheral Arterial Tonometry) Index is calculated automatically by the built-in software. The RH-PAT Index is the ratio between the mean pulse-wave amplitude, calculated between 90 and 120 s after releasing the occlusion, and mean pulse-wave amplitude during the 210 s preceding the occlusion. In order to eliminate confounding systemic neurovegetative vasomotor effects, this index is normalised with regard to the contralateral side.

*The WELCH (Walking Estimated Limitation Calculated by History) questionnaire* is a self-administered questionnaire validated in French and specific to PAD [22]. Via four questions (‘duration of slow walking’ , ‘duration of moderate walking’ , ‘duration of fast walking’ , ‘comparison of one’s walking speed with that of one’s entourage’), it evaluates the symptoms of the claudication in everyday life. It takes about 5 min to complete the questionnaire.

### Sample size calculation and statistical analysis

According to our pilot study [21], the expected benefit is an improvement of 25% in walking distance without pain in the TENS group compared with the placebo group at 3 weeks. Considering a mean value of the principal criterion of 300 m in patients in the SHAM group, with a standard deviation of 105 m common to both groups, a power of 90% with a bilateral hypothesis and an alpha risk of 5%, a difference of 25% in the walking distance between the two groups at the end of the study (that is to say a mean value of 300 m versus a mean value of 375 m), it is necessary to include 42 subjects per group. This number will be increased to 50 subjects per group (100 subjects altogether) to take into account an estimated 15% premature exit from the study.

Analysis of objective differences will be based on an analysis of covariance (ANCOVA) of the evolution of judgement criteria (adjusted for their initial value) rather than a simple comparison of values at the end of the follow-up. These ANCOVA models should increase the power of analyses concerning the above data [26]. After a description of the initial characteristics of the included subjects (for the whole population and by group), and after verification of the initial comparability of the two groups (numbers, percentages, mean ± standard deviation, or median and range), evaluation of the efficacy of the intervention will be made as a single analysis, on an intention-to-treat basis (according to the group attributed by randomisation), with a global alpha risk of 5%, a bilateral formulation of the statistical tests, normality of distribution and the homogeneity of variances will be evaluated graphically and by the Shapiro-Wilk and the Fisher-Snedecor normality tests. In cases of non-normal distributions, we will attempt to normalise data using appropriate transformations.

Analysis of the of principal judgement criterion: the evolution of the claudication distance between the start and the end of the study in the two intervention group (TENS versus SHAM) will be compared using ANCOVA adjusted for initial walking distance.

Analyses of the secondary judgement criteria: according to the same principles as the principal criterion, an ANCOVA according to the intervention group (TENS versus SHAM) adjusted for the initial value of the judgement criterion will be used for each of the criteria.

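### The primary ANCOVA adjusts only for a baseline distance that the test calibrates towards 300 m, so it will probably add little power; the calibrated speed and slope, which carry severity, are left out

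*Protocol article*

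**What the plan says.** Three parts of the protocol article bear on this.

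- **The test (300-m treadmill test).** Speed and slope are set for each patient over five pre-tests, "adjusted in such a way to make claudication develop at a distance of 300 m". The result is an individual setting, "with a baseline speed of X km/h and a baseline slope of X"%, which then stays fixed for every evaluation before and after treatment. The baseline evaluation follows at least 1 h after the pre-tests and consists of five successive walks.
- **The analysis (Sample size calculation and statistical analysis).** The change in claudication distance is compared between arms by ANCOVA with initial walking distance as the covariate. No other covariate is named. ANCOVA is preferred to a plain comparison of final values because "These ANCOVA models should increase the power of analyses concerning the above data". The same approach is applied to each secondary criterion.
- **The sample size (same section).** It is a comparison of two means, "that is to say a mean value of 300 m versus a mean value of 375 m", "with a standard deviation of 105 m common to both groups", with "a power of 90% with a bilateral hypothesis and an alpha risk of 5"%. From this, "it is necessary to include 42 subjects per group", raised to 50 for 15% premature exit.

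**The concern.** ANCOVA gains precision only to the extent that the covariate varies between patients and that this variation predicts the outcome. The 300-m test is built to remove most of the variation between patients in baseline distance. A patient with mild claudication and one with severe claudication should both start near 300 m, but at different speeds and slopes. Table 1 divides stage II at a walking distance of 200 m, and both substages are eligible, so severity will differ between patients.

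The model thus adjusts for the quantity that calibration has largely stripped of severity and omits the quantities into which calibration has moved it. Two things are at stake for the primary outcome: whether the stated reason for ANCOVA applies to it, and whether precision that the trial's own data could provide is left unused. A chance imbalance in severity between arms would also hardly show in the baseline distance, so the planned adjustment could not correct it.

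**Working it through.** **Inputs from the sample size paragraph:** difference 375 − 300 = 75 m; SD 105 m; two-sided alpha 0.05; power 0.90; 1:1 allocation; 15% exit.

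**Inputs not in the document, so assumed:** SD of the baseline (D0) distance, 0 to 60 m; regression slope b of D21 distance on D0 distance, 0 (scatter is pure noise) to 1 (scatter persists in full); share R² of D21 variance explained by speed and slope, 10% to 25%.

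**Step 1. Reproduce the plan's figure.** n = 2 × [105 × (1.960 + 1.282) / 75]² = 41.19, rounded up to 42. With exit, 42 / 0.85 = 49.4, rounded up to 50. Both figures reproduce with no allowance for ANCOVA. Power at 42 per group is 90.5% by the normal approximation and 89.9% by the noncentral t distribution.

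**Step 2. Gain from adjusting for D0 distance.** With D0 in the model, the treatment effect is the same whether the response is the change or the D21 value, so the D21 SD of 105 m applies. The correlation is rho = b × SD(D0) / 105, and the residual SD is 105 × √(1 − rho²).

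| SD of D0 | b | rho | variance removed | n per group | power at 42, normal | power at 42, t |
|---|---|---|---|---|---|---|
| any | 0 | 0 | 0% | 42 | 90.55% | 89.88% |
| 10 m | 1 | 0.095 | 0.9% | 41 | 90.80% | 90.14% |
| 20 m | 1 | 0.190 | 3.6% | 40 | 91.53% | 90.91% |
| 30 m | 0.5 | 0.143 | 2.0% | 41 | 91.10% | 90.46% |
| 30 m | 1 | 0.286 | 8.2% | 38 | 92.73% | 92.15% |
| 45 m | 1 | 0.429 | 18.4% | 34 | 95.18% | 94.74% |
| 60 m | 1 | 0.571 | 32.7% | 28 | 97.88% | 97.62% |

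Up to a D0 SD of 30 m the gain is at most about 2 points (92.73 − 90.55 = 2.18; 92.15 − 89.88 = 2.27). For comparison, a freely varying baseline with rho of 0.5 to 0.7 would bring n down to between 31 and 22.

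**Step 3. Possible gain from speed and slope.** Residual SD is 105 × √(1 − R²); power by noncentral t at 42 per group.

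| assumed R² | residual SD | fall in SE | power |
|---|---|---|---|
| 0 | 105.0 m | 0% | 89.9% |
| 10% | 99.6 m | 5% | 92.6% |
| 20% | 93.9 m | 11% | 95.1% |
| 25% | 90.9 m | 13% | 96.2% |

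**Step 4. Cost if speed and slope explain nothing.** Going from 82 to 80 error degrees of freedom costs about 0.02 points (89.88% to 89.86%). Useless covariates also inflate the variance slightly through chance correlation with the arm. The expected factor for two is 1 + 2/(82 − 2 − 1) = 1.025, which takes power to about 89.1%. An R² of roughly 2.5% is enough to cancel this.

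**The case against.** The case for leaving the plan alone has real substance.

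- **The D0 distance is not the calibration target itself.** It is measured afresh at least 1 h later, over five walks, and may scatter around 300 m. A reader might infer that the power gain is exactly zero. The document does not support that: it gives neither the D0 SD nor the correlation with D21, and Step 2 shows a material gain once persistent scatter reaches about 45 m. This stands; the defensible word is *likely small*.
- **The power sentence is general.** It covers the judgement criteria as a whole. Peak VO₂, lipids, HbA1c, the WELCH score and others are not calibrated to a common value, and a gain there is plausible. This stands, so the criticism is confined to the primary outcome.
- **No design figure depends on the gain.** The 42 per group takes no credit for ANCOVA. A reader might infer that the trial is underpowered; it is not, under its own assumptions. This stands.
- **Leaving out a prognostic covariate does not bias a randomised comparison.** A reader might infer a biased effect or an inflated type I error from an uncorrected imbalance in severity. Neither follows: chance imbalance is already reflected in the standard error. This stands.
- **Setting the workload individually already normalises for severity**, so speed and slope may predict little of the D21 distance. This is possible, and the document gives no figure either way. It makes the gain from the fix uncertain, but Step 4 shows that little is lost if the objection is right.
- **Further covariates could be left to the analysis plan.** True in general. Here, though, the article states the primary model and gives a reason for it, and for this outcome that reason sits badly with the article's own test.

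**Conclusion.** The point holds in a limited form. For the primary outcome, the sole covariate is compressed by design, and adjustment for it is likely to add little power: nil if the scatter around 300 m is noise, and about 2 points at most with a D0 SD up to 30 m. It would add more only if D0 scatters by about 45 m or more and the scatter persists to D21. These limits rest on an assumed slope between 0 and 1 and on the plan's SD of 105 m. The document cannot settle where in the range the trial will fall.

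The consequence is forgone precision and weaker protection against chance imbalance in severity. The planned ANCOVA remains valid and unbiased, and the sample size and stated power are unaffected. The possible improvement, to between 92.6% and 96.2% power, rests wholly on an assumed R² of 10% to 25%. The change is worth making because it is cheap, not because the plan fails without it.

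**What to change.** 1. In the primary ANCOVA, pre-specify the calibrated baseline treadmill speed and slope, or the single workload they imply, as covariates beside the D0 distance.
2. Limit the sentence on increased power to the criteria whose baseline is not calibrated.

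The cost is a line or two of analysis text and one or two degrees of freedom; the small loss if the covariates prove uninformative is shown in Step 4. No new data are needed, because each patient's settings must be kept in order to repeat the test at D21. The sample size does not change. The article states that recruitment has not started, so the covariates can be fixed before any outcome is seen; added after unblinding, they would look post hoc.

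### Randomisation is stratified by centre but the stated ANCOVAs leave centre out; if centre is prognostic, the reported standard error is too large and some precision is lost

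*Protocol article*

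**What the plan says.** Under Blinding and randomisation, the protocol article sets a 1:1 allocation and names one stratification factor: "The randomisation will be stratified according to the four inclusion centers". Within each centre the arms are "distributed in random-sized blocks (blocks of 2, 4 or 6").

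Under Sample size calculation and statistical analysis, it names the models. The primary comparison of the change in claudication distance "will be compared using ANCOVA adjusted for initial walking distance". Each secondary outcome follows the same principle, with an ANCOVA by arm "adjusted for the initial value of the judgement criterion will be used for each of the criteria". Centre appears in none of these models. The same section explains why ANCOVA was chosen: "These ANCOVA models should increase the power of analyses concerning the above data".

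The sample size rests on "a mean value of 300 m versus a mean value of 375 m", a common standard deviation of 105 m, 90% power and a two-sided 5% test. This gives 42 per group, raised to 50 for 15% premature exit.

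**The concern.** Blocking within centre forces the arms to be nearly balanced in every centre. Differences between centres in average outcome therefore almost cancel from the treatment contrast, and its true variance is close to the within-centre variance. A model without centre does not know this. It leaves the centre differences in the residual and computes its standard error from the larger, total variance.

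If centre is prognostic, the reported standard error overstates the true one, intervals are wider than they need to be, and the test rejects less often than its nominal 5% under the null. The design would have paid for stratification and the analysis would not collect the benefit, although the article chooses ANCOVA in order to gain power.

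What is at stake is the precision and calibration of the reported interval and p-value, not the validity of the comparison.

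**Working it through.** **Inputs from the protocol article.** Difference 375 − 300 = 75 m; SD 105 m; two-sided alpha 5%; power 90%; 42 per group before dropout; four centres; blocks of 2, 4 or 6.

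**Assumptions not in the article.** v is the share of outcome variance, after baseline adjustment, that is due to centre; values of 0, 5, 10 and 20% are tried. The SD of 105 m is taken as the SD after baseline adjustment, so baseline is given no credit for reducing variance.

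**Step 1: reproduce the plan's figure.** n per group = 2 × (1.96 + 1.2816)² × 105² / 75² = 2 × 10.51 × 1.96 = 41.2, rounded up to 42. Then 42 / (1 − 0.15) = 49.4, rounded up to 50. Both agree with the article. Power at 42 per group is 90.5% by the normal approximation and 89.9% by the t distribution.

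**Step 2: standard error with and without centre.**
- Without centre, the model reports SE₀ = 105 × √(2/42) = 22.91 m.
- With centre, SE₁ = 22.91 × √(1 − v). Under centre-stratified blocking this is also close to the true SD of the estimate from either model.
- Overstatement of the SE = 1/√(1 − v) − 1.
- Actual alpha without centre = 2 × [1 − Φ(1.96/√(1 − v))].
- Power without centre = Φ((75 − 1.96 × 22.91)/SE₁).
- Power with centre = Φ(75/SE₁ − 1.96).

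Example at v = 10%: SE₁ = 22.91 × 0.9487 = 21.74 m; overstatement 5.4%; alpha = 2 × [1 − Φ(2.066)] = 3.9%; power without centre = Φ(30.1/21.74) = 91.7%; power with centre = Φ(3.450 − 1.960) = 93.2%.

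| v | SE with centre (m) | SE without centre too large by | Alpha without centre | Power without | Power with |
|---|---|---|---|---|---|
| 0% | 22.91 | 0% | 5.0% | 90.5% | 90.5% |
| 5% | 22.33 | 2.6% | 4.4% | 91.1% | 91.9% |
| 10% | 21.74 | 5.4% | 3.9% | 91.7% | 93.2% |
| 20% | 20.49 | 11.8% | 2.8% | 92.9% | 95.5% |

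**Step 3: check by simulation.** 84 patients, four centres, blocks of 2/4/6, 5,000 runs per scenario. The Monte Carlo standard error of an alpha near 5% is √(0.05 × 0.95/5000), about 0.3 points.

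| Centre sizes | v | True SD of estimate, no centre (m) | Reported SE, no centre (m) | Alpha without / with | Power without / with |
|---|---|---|---|---|---|
| 21 each | 0% | 22.71 | 23.00 | 4.4 / 4.5% | 89.4 / 89.4% |
| 21 each | 5% | 22.48 | 23.02 | 4.3 / 4.9% | 89.6 / 90.3% |
| 21 each | 10% | 21.98 | 23.02 | 3.6 / 4.8% | 90.4 / 91.8% |
| 21 each | 20% | 20.64 | 23.09 | 2.8 / 5.2% | 91.4 / 94.8% |
| 40/24/12/8 | 10% | 22.24 | 23.01 | 4.4 / 5.4% | 90.4 / 92.2% |
| 40/24/12/8 | 20% | 20.84 | 23.02 | 2.7 / 5.0% | 91.9 / 94.9% |

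The direction and approximate size match Step 2. With no centre effect and equal centres, adding centre leaves the average SE essentially unchanged (23.00 against 23.02 m).

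**Step 4: allow for dropout.** With 100 randomised and 15 lost at random (4,000 runs per scenario), balance within centre is disturbed. Alpha without centre is then about 4.2 to 4.3% at v = 10% and 3.2 to 3.4% at v = 20%. At v = 5% it cannot be told from 5% (4.8 to 5.3%, Monte Carlo error about 0.35 points).

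**The case against.** **The loss is conditional.** A reader might infer from the mismatch alone that the standard error is too large and that power is lost. The article does not support that as a statement of fact: it gives no between-centre variance, and at v = 0 nothing material is lost. This stands, and the point is worded accordingly.

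**Centre may matter little here.** Treadmill speed and slope are set for each patient so that claudication appears at 300 m, then held constant. This should largely remove centre differences in starting distance. It does not remove differences in response over three weeks of locally delivered rehabilitation. It also means that initial distance varies little, so it can hardly stand in for centre. The calibration argues for caution about a large v without showing that v is zero. That one centre is overseas is no evidence of size either.

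**The 20% row is the extreme.** At 5% and 10% the power gain is only about 1 and 1.5 points, and dropout brings alpha a little nearer to 5%. Both stand.

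**The article is condensed.** It never says that baseline is the sole covariate, and an analysis plan could add centre. But it does name the adjustment for the primary outcome and repeats the same single covariate for every secondary outcome. An analysis plan that follows this text would omit centre, so this is a stated choice rather than a silence.

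**Conclusion.** The mismatch is certain: the only stratification factor is absent from every model described. The consequence is conditional and modest. If centre explains 0, 5, 10 or 20% of the variance left after baseline adjustment, the reported SE is about 0, 3, 5 or 12% too large, and the test runs at about 5, 4.4, 3.9 or 2.8%, slightly closer to 5% after dropout. Adding centre gains about 0, 1, 1.5 or 3 points of power.

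Three stronger readings should be resisted. The treatment estimate is not biased. Type I error is not inflated, since the error runs the conservative way. The trial is not made underpowered: with a total SD of 105 m, power without centre is 90.5 to 92.9% by formula and about 89 to 92% in simulation, against a planned 90%, and the 42 per group is unaffected.

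The figures rest on the assumed centre shares and on 105 m as the SD after baseline adjustment. This is a low-cost gain in precision, not a threat to validity.

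**What to change.** State in the analysis section that the primary ANCOVA and every secondary ANCOVA include centre as a fixed effect with four levels: outcome ~ group + baseline value + centre.

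The cost is one sentence and 3 degrees of freedom. With 84 analysed, the residual degrees of freedom fall from 81 to 78 and the critical t value moves from 1.990 to 1.991. The sample size does not change. The Trial status section says that recruitment has not started, so the change can be made before any data exist.
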